## Abstract

**Background:**

Nocturnal hemodialysis (NHD) is an alternative to conventional three times per week hemodialysis (CvHD) and has been reported to improve several health outcomes. To date, no randomized controlled trial (RCT) has compared NHD and CvHD. We have undertaken a multi-center RCT in hemodialysis patients comparing the effect of NHD to CvHD on left ventricular (LV) mass, as measured by cardiac magnetic resonance imaging (cMR).

**Methodology/design:**

All patients in Alberta, Canada, expressing an interest in performing NHD are eligible for the study. Patients enrolled in the study will be randomized to either NHD or CvHD for a six month period. All patients will have a full clinical assessment, including collection of biochemical and cMR data at baseline and at 6 months. Both groups of patients will be monitored biweekly to optimize blood pressure (BP) to a goal of <130/80 mmHg post-dialysis using a predefined BP management protocol. The primary outcome is change in LV mass, a surrogate marker for cardiac mortality, measured at baseline and 6 months. The high sensitivity and reproducibility of cMR facilitates reduction of the required sample size and the time needed between measures compared with echocardiography. Secondary outcomes include BP control, anemia, mineral metabolism, health-related quality of life, and costs.

**Discussion:**

To our knowledge, this study will be the first RCT evaluating health outcomes in NHD. The impact of NHD on LV mass represents a clinically important outcome which will further elucidate the potential benefits of NHD and guide future clinical endpoint studies.

## Background

Despite advances in dialysis therapy, mortality and morbidity remain high for patients with end-stage renal disease (ESRD). For instance, the mortality of this very high-risk population remains at nearly 20% per year with death rates from cardiac disease that are 10–20 fold higher in dialysis patients than in the general population [1]. Only 16% of incident dialysis patients have normal hearts by echocardiography, with concentric left ventricular hypertrophy (LVH) present in 41% and systolic failure in 16% [2]. This is important since the presence of LVH is associated with a several fold increase in risk for both heart failure and mortality [2,3].

Randomized trials that have attempted to demonstrate reduction in mortality among dialysis patients have generally been unsuccessful [4-8]. Even trials designed to impact surrogate endpoints, such as regression of LVH or LV dilatation, have been disappointing. Furthermore, there are very few interventions that have been shown to improve the poor health-related quality of life (HRQOL) observed in this population.

This difficulty of improving health outcomes may be due to the fact that ESRD is characterized by numerous complex metabolic and physiological abnormalities. Conventional hemodialysis (CvHD) does not normalize the majority of these abnormalities, and provides only a small fraction small molecular weight solute clearance compared with native kidney function[9]. In an attempt to improve urea clearance and clinical outcomes, nocturnal hemodialysis (NHD), a technique first developed in the 1970s, has received renewed attention. In NHD, patients perform dialysis at home; this is done five to six nights per week while they sleep.

Case control and cohort studies suggest that nocturnal hemodialysis may induce regression of LVH [10-12], improve HRQOL [13-15], and improve blood pressure control [16-18], among other health benefits. However, observational data may lead to conclusions ultimately refuted by randomized clinical trials (RCT). Given the uncertainty associated with the observed outcomes and costs derived from non-randomized studies examining NHD [19,20], it is important to have high quality data on NHD before widespread uptake of this new therapy occurs. We describe a randomized pilot trial comparing NHD (5 or 6 nights per week, 8 hours per night) and conventional hemodialysis (three times per week, four hours per session) with respect to their effect on progression of left ventricular mass measured by cardiac magnetic resonance imaging (cMR). Data on health-related quality of life, and measures of physiologic control, including blood pressure, anemia, calcium and phosphate metabolism and costs will be assessed as secondary outcomes.

## Methods/design

This study will be a prospective, two-center, parallel-group randomized, controlled study, with blinding of outcome assessors and data analysts. Approval has been granted by the local bioethics committees at the University of Calgary and the University of Alberta.

Eligible patients are men or women greater than 18 years of age who are currently receiving any hemodialysis modality (in-center, self-care or home) excluding current NHD. To be enrolled in this study, patients must be interested in and willing to train for NHD. Exclusion criteria include the inability to perform NHD due to physical or mental incapacity or the inability to provide informed consent.

Those patients meeting the inclusion and exclusion criteria will be randomized to either the NHD or control group. Randomization will be performed using a computer generated sequence in blocks of four patients. Randomization will be stratified by center and by baseline dialytic modality (self-care/home hemodialysis vs. in-center hemodialysis). Concealment will be assured through the use of sealed, opaque envelopes. Given the logistics of training patients within a nocturnal dialysis program, randomization will occur at one time point for patients willing to enter the study; however, patient entry into the study (i.e. the baseline study visit) will be staggered over time to facilitate NHD training in an orderly fashion. This will create a similar number of intervention and control patients at any given time point. This approach will be used to avoid an imbalance in drop-out rates between the two groups. Subjects randomized to CvHD will be eligible to commence NHD after study exit (six months).

### Objectives

The primary objective of this study is to evaluate the impact of NHD on the change in LV mass compared to CvHD in ESRD patients. LV mass will be measured by cMR at baseline and after six months of study and the difference will be compared between groups.

Secondary objectives of this study include the evaluation of NHD, as compared to CvHD, on (1) blood pressure, (2) HRQOL, (3) anemia, (4) mineral metabolism, and (5) health care and non-health care-related costs.

### Procedures – General considerations

Two centers in Alberta, Canada, the University of Calgary and the University of Alberta, will actively participate in the study. The first patient was enrolled in August 2004 and by January 2006 enrollment is expected to be complete. All patients will be followed for a period of six months for the primary and secondary objectives. Given the nature of the intervention, it is not possible to blind patients and investigators to the study intervention; however, the radiologists assessing the cMR studies (i.e. outcome assessors) and data analysts will be blinded to patient allocation.

Formal study visits will occur at study entry and at six months (study exit). These will be performed by physicians involved in the study and will be comprised of questionnaires, standardized blood pressure measurements, and reviews of recent dialysis sessions and laboratory work (see Table 1). Entry and exit visits will be performed within one week of entry and exit cMR tests. The baseline study visit will occur immediately pre-dialysis on a mid-week dialysis day for both groups. Exit study visits will occur immediately pre-dialysis on a mid-week dialysis day for the CvHD patients and ~9 hours post-dialysis (~5 hours predialysis) for NHD patients.

**Table 1 T1:** Data collection time points.

Data Collected	Month of Study							
	Randomization	Baseline	1	2	3	4	5	6

Baseline Characteristics		**X**						**X**
Comorbidity Data		**X**						
cMR		**X**						**X**
Blood Pressure		**X**						**X**
HRQOL	**X**	**X**						**X**
Hbg/Hct		**X**	**X**	**X**	**X**	**X**	**X**	**X**
Erythropoeitin		**X**	**X**	**X**	**X**	**X**	**X**	**X**
Calcium/Phosphate		**X**	**X**	**X**	**X**	**X**	**X**	**X**
PTH		**X**						**X**
Medications		**X**	**X**	**X**	**X**	**X**	**X**	**X**
Kt/V		**X**						**X**
Economic Data		**X**						**X**

### Procedures – Nocturnal hemodialysis

Patients will initially be trained in-center for four to five days per week with direct nursing supervision and monitoring of biochemical parameters. During this training period dry weight and medications will be adjusted as dictated by blood pressure and biochemical parameters. Target weight will be adjusted over the course of the first 4 weeks to achieve a goal postdialysis blood pressure of 130/80, with introduction and discontinuation of blood pressure medications according to the protocol outlined below and in Figure 1. Anemia management will be carried out according to a standardized nursing-led anemia protocol aiming for a goal hemoglobin of 110 – 120 g/L utilizing erythropoietic stimulating proteins and iron supplements as necessary [21]. Mineral metabolism management will be carried out by the patient's attending nephrologist according to local treatment goals (calcium < 2.55 mmol/L, phosphate <1.80 mmol/L and intact PTH 150 – 300 ng/L).

**Figure 1 F1:**
[figure not shown]
Blood pressure management algorithm.

Upon completion of training, nocturnal hemodialysis will be performed by the patients, at home, without remote monitoring 5 – 6 nights per week for a minimum of 6 hours per night. Dialysis will be performed with blood flow rates of 250 ml/min in patients receiving dialysis by central venous catheter or 150–200 ml/min in patients dialyzing by a single needle, button-hole technique in a graft or fistula. Dialysate flow rates of 300 ml/min were used for all patients.

### Procedures – Conventional hemodialysis

Patients will continue their pre-randomization dialysis modality (in-center, self-care or home hemodialysis) and dialysis prescription. Blood pressure management will be standardized as outlined below and in Figure 1. Anemia and mineral metabolism management will be carried out as per the protocols noted above for the NHD patients.

### Procedures – Blood pressure treatment

Blood pressure and antihypertensive medication use are potentially important determinants of LVH. In an attempt to assess whether the hypothesized impact of NHD on LV mass is due to improved BP control or to a non-BP related effect, both arms of the study will be aggressively treated to a post-dialysis blood pressure goal of 130/80 mmHg. This goal will be achieved by implementation of a management algorithm (see Figure 1). Although there is controversy as to the goal BP in hemodialysis patients [22], and in addition, whether pre- or post- dialysis pressures correlate best with cardiovascular outcomes, for the purposes of this algorithm, the blood pressure of interest will be the recording obtained by the dialysis machine's automated blood pressure cuff immediately post-dialysis. Blood pressures will be reviewed and appropriate changes made as per the blood pressure algorithm every two weeks. Antihypertensive medications previously prescribed by the patients' nephrologist will be left in place at study entry. The protocol mandates stepwise reductions in dry-weight as tolerated by the patient before intensification of their pharmacologic routine. Pharmacologic intervention is preferentially accomplished by first increasing doses of already prescribed angiotensin-converting enzyme inhibitors or angiotensin receptor blockers followed by beta blockers or calcium channel blockers, and then other antihypertensives. The use of direct vasodilators will be avoided when possible. If these manipulations are not successful in achieving target blood pressure other agents may be added.

### Outcomes – Left ventricular mass

LV mass, in grams, will be measured by cMR at baseline and at month six for patients in both arms of the study. MR imaging will be performed in each patient using a 1.5-T system (Sonata Software versions Syngo 2002B and 2004A; Siemens Medical Solutions, Erlangen, Germany). ECG gating will be used for all acquisitions. Briefly, routine localizers will be obtained and a four chamber localizer will be used. By using the end-diastolic cine frame of this four-chamber view, a series of parallel short-axis image planes can be defined, starting at the base of the LV and right ventricle (RV) and encompassing the entire LV and RV from base to apex. The most basal image plane will be positioned well into the atria. This will also ensure that the most basal part of the ventricles will be covered. The entire LV/RV will be covered with 10–12 slices (10 mm thick, gap 2 mm). At every short-axis plane, a breath-hold cine acquisition will be performed. For cine imaging, a steady-state free precession pulse sequence will be applied with 15 ky lines per heartbeat. Retrospective gating will be used with an acquisition window of 20% greater than the average RR interval and 20 phases will be calculated per RR interval. The field of view will be adapted to the individual patient to obtain optimal images. Data will be analyzed using vendor provided software (Argus, Siemens Medical Solutions, Erlangen, Germany). Endocardial, epicardial and papillary muscle outlines will be manually traced on end systolic and end diastolic frames. Ejection fraction, LV mass, and stroke volume will be calculated.

### Outcomes – Blood pressure

Assessment of the blood pressure outcomes will be performed at baseline and month six of the study by a study physician using a mercury sphygmomanometer following the CHEP protocol for blood pressure measurement [23]. A five-minute rest in a quiet, comfortable room will be used prior to measurement. Three blood pressure measurements will be taken five minutes apart with the average of the last two blood pressures used as the true blood pressure.

Blood pressure control will also be evaluated by the mean change in blood pressure parameters (systolic, diastolic, mean arterial, and pulse pressure). The use of antihypertensive medications will also be assessed at both the entrance and exit visit and the change in the mean number of antihypertensive medications will be compared between the NHD and CvHD group.

### Outcomes – Health related quality of life

Health-related quality of life questionnaires will be administered at the time of randomization (before patients are aware of their treatment allocation), at baseline (i.e. month 0), and at three and six months of the study. Consistent with published guidelines [24], HRQOL will be assessed using a spectrum of HRQOL instruments including a disease specific questionnaire (Kidney Disease Quality of Life Short Form (KDQOL-SF), a generic questionnaire (Short-Form 36 (SF-36), and a preference-based questionnaire (Euroqol (EQ-5D)) [25,26].

The EQ-5D will be used in this study as a preference-based index measure to approximate utility scores. Questions in the EQ-5D index focus on five dimensions: mobility, self-care, usual activities, pain/discomfort and anxiety/depression. The EQ-5D Index, based on health state valuations elicited from the general public [27,28] is anchored at 0.0 (dead) and 1.0 (full health). A minimum increment of 0.03 in the EQ-5D index score can be considered clinically important as it corresponds to the smallest coefficient for a change from 'No problem' to 'Some problems' within a dimension of the EQ-5D (26). Given that the EQ-5D measures overall quality of life, the EQ-5D index score will be the primary measure used to determine whether NHD has an impact on HRQOL.

The KDQOL-SF includes questions targeted at particular health-related concerns for individuals on dialysis. Scores on each KDQOL-SF dimension range from 0 – 100, with higher scores reflecting better HRQOL. The generic HRQOL profile measure used in this study will be the SF-36, which has been used in ESRD [29] and includes eight multi-item scales describing general HRQOL issues. As with the KDQOL-SF, scores on each dimension can range from 0 – 100, with higher scores reflecting better HRQOL. These measures will predominantly be measured to determine which facets of HRQOL are most impacted by NHD.

### Outcomes – Anemia

Hemoglobin and hematocrit will be measured every month throughout the study. The dose of erythropoietic stimulating proteins and iron supplements will be recorded for two months prior to starting the study as well monthly for the duration of the study. The effect of the intervention on anemia management will be primarily assessed using the change in mean erythropoietin/hematocrit ratio. As well, since both groups may obtain similar hemoglobin levels by the use of erythropoietin and iron, the average doses of these medications for the two months before study entry and the last two months of the study will also be compared between groups.

### Outcomes – Mineral metabolism

Calcium, phosphate, and albumin levels will be measured monthly throughout the study. PTH levels will be drawn at baseline and study exit. Information on the dose and type of phosphate binder, and the dose, type and route of administration for vitamin D analogs will be recorded monthly throughout the study.

### Outcomes – Costs

To enable economic evaluation of NHD, use of health care resources and their associated costs will be collected prospectively alongside the clinical trial. Costs to be assessed will include the costs associated with NHD, including the cost of training patients, the cost of necessary renovations to a patient's home, the cost of the hemodialysis machine, and the ongoing cost of supplies and clinical support. The cost of providing dialysis for patients in the conventional hemodialysis group will be assessed as previously described [30]. In addition to collecting dialysis-specific costs, we will also collect information for all patients on associated health care costs including the cost of hospitalization, the cost of outpatient day surgery (including access surgery), the cost of diagnostic imaging (including that required to maintain the patient's vascular access), the cost of medications, and the cost of laboratory testing [30]. Lastly, patients will complete a questionnaire at study entry and exit to assess the non-health care related costs associated with performing nocturnal and conventional dialysis.

### Statistical considerations

This will be a superiority study undertaken to test the hypothesis that NHD leads to less LV mass progression compared to CvHD. Based upon observational data obtained by echocardiography (11), the baseline LV mass for both groups will be 147 +/- 8 g. To give the study the power (1-beta = 0.95) to detect a significant (alpha = 0.05, two-tailed test) 10 g difference in LV mass (a clinically important and statistically detectable difference given the use of CMR) between the 2 treatment groups, 32 patients are needed to complete the study. Assuming 20% dropout (due to transplantation or death over six months), 19 patients in each arm of the study will be enrolled.

All analyses will be undertaken by a data analyst blinded to the subject treatment assignment. Summary statistics will be used to describe the baseline characteristics of both groups. For the primary endpoint of change in LV mass, the intention-to-treat (ITT) approach will be used, including all enrolled patients who have at least one cMR measurement. The analysis of the primary end-point will be based on the difference between the groups in the change of LV mass over the study period. For patients who drop-out of the study (death or renal transplant) before the final cMR examination, we will assume no change in the baseline cMR parameters for the primary ITT analyses. This very conservative approach will likely bias the final results towards the null hypothesis. A similar approach will be used for the secondary endpoints (Table 2). Exploratory secondary analyses will be performed using an observed cases approach.

**Table 2 T2:** Primary analyses for primary (LV mass) and secondary outcomes

Factor	First Measure	Final Measure	Primary Analysis*
LV mass	Baseline	6 month visit	Comparison of mean change in LV mass for NHD vs control subjects
Blood pressure	Baseline visit – average of 5 and 10 minute readings	6 month visit – average of 5 and 10 minute readings	Comparison of mean change in systolic BP for NHD vs control subjects
Quality of Life	Baseline	6 month visit	Difference in the 6 month and baseline EQ-5D index scores for NHD vs control group – intention to treat, last observation carried forward
Anemia	Mean Hct and Epo administered for two months preceding baseline visit	Mean Hct and Epo administered for the final two months of the study	Mean change in hct/epo ratio for NHD vs control subjects
Mineral Metabolism	Mean Ca*PO4 for two months preceding baseline visit	Mean Ca*PO4 for the final two months of the study	Mean change in Ca*PO4 for NHD vs control subjects

*All randomized subjects with at least one measurement are included.

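### The 95% power claim rests on the spread of baseline echocardiographic LV mass, not on the SD of the 6-month cMR change that will be analysed, so it is unsupported in either direction

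*Protocol article*

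**What the plan says.** All inputs to the sample size stand in the first paragraph of Statistical considerations in the protocol article.

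- Variability: "Based upon observational data obtained by echocardiography (11), the baseline LV mass for both groups will be 147 +/- 8 g". The plus-minus figure is not labelled as a standard deviation or a standard error.
- Target: "To give the study the power (1-beta = 0.95) to detect a significant (alpha = 0.05, two-tailed test) 10 g difference in LV mass".
- Result: "32 patients are needed to complete the study", that is 16 per arm.
- Enrolment: "Assuming 20% dropout (due to transplantation or death over six months), 19 patients in each arm of the study will be enrolled".

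The next paragraph says that the primary analysis is "based on the difference between the groups in the change of LV mass over the study period", and Table 2 repeats this as a comparison of mean change. The section on the LV mass outcome specifies cMR at baseline and at month six. The article gives no SD of change, no correlation between the two measurements and no figure for cMR variability.

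**The concern.** The sample size for a comparison of mean change depends on the SD of the change within patients. The article supplies the spread of a single baseline measurement instead, taken with a different imaging method from an observational source. The two quantities can differ in either direction, depending on how strongly the 6-month value follows the baseline value.

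The figure is also small for a spread between patients. It is about 5% of the mean, whereas the Background describes a very mixed population: "Only 16% of incident dialysis patients have normal hearts by echocardiography, with concentric left ventricular hypertrophy (LVH) present in 41" per cent, with systolic failure in a further 16%. A spread that narrow makes one ask whether 8 g is a standard error.

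This single input drives both the number of patients and the way a null result on the primary endpoint would be read. If the SD of change is well above 8 g, failure to show a 10 g difference would say much less than a claim of 95% power suggests.

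**Working it through.** **Inputs from the article.** Difference 10 g; two-sided alpha 0.05; power 0.95; 16 completers per arm; spread 8 g around a mean of 147 g.

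**1. Reproducing the plan's figure.** With SD = 8 g and the normal approximation:

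n per arm = 2 × (1.960 + 1.645)² × (8/10)² = 16.6

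This rounds up to 17 per arm (34 in total), against the stated 16 per arm (32). A t-test calculation needs 18 per arm (36). At 16 per arm the power is 0.942 by the normal approximation and 0.928 by the noncentral t. The SD that gives exactly 16 per arm is 10 / (√(2/16) × 3.605) = 7.85 g. Other settings fit less well: one-sided alpha, or 90% power, gives 28 in total, and 80% power gives 22. Direct use of 8 g as the SD is therefore the likeliest route to 32, but the match is approximate.

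**2. When 8 g would be the right SD.** If 8 g is a between-patient SD, equal at both times, and r is the correlation between baseline and 6 months, then

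SD of change = 8 × √(2(1 − r))

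This equals 8 g only at r = 0.5. The article gives no r, so the values below are assumptions. Power is by the noncentral t, 16 per arm, 10 g difference.

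| r (assumed) | SD of change | Power |
|---|---|---|
| 0.2 | 10.1 g | 0.77 |
| 0.5 | 8.0 g | 0.93 |
| 0.8 | 5.1 g | above 0.99 |

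**3. How narrow 8 g is as a between-patient SD.** 8/147 = 5.4%. The range 147 ± 1.96 × 8 is 131 to 163 g for about 95% of patients.

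**4. Larger SDs of change, for illustration only.** None of these SDs comes from the article. Power is by the noncentral t, as above. The last column is the difference detectable with 95% power at 16 per arm by the normal approximation: SD × √(2/16) × 3.605 = 1.2745 × SD.

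| SD of change (assumed) | Power for 10 g | Detectable difference |
|---|---|---|
| 8 g | 0.93 | 10.2 g |
| 12 g | 0.63 | 15.3 g |
| 15 g | 0.45 | 19.1 g |
| 20 g | 0.28 | 25.5 g |
| 25 g | 0.20 | 31.9 g |

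**The case against.** The strongest reply is that the error may be harmless or even favourable. If 8 g is a true between-patient SD, any correlation above 0.5 makes the plan conservative. The abstract presents cMR as sensitive and reproducible enough to reduce the sample size, and the sample size paragraph refers to a "10 g difference in LV mass (a clinically important and statistically detectable difference given the use of CMR) between the 2 treatment groups". Both suggest less measurement noise than with echocardiography. This stands as far as direction goes: the article does not show that the trial is underpowered. It does not restore the 95% figure, because no cMR precision enters the calculation.

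A reader might infer that 8 g is a standard error and that the trial therefore has little chance of detecting 10 g. The article does not support that conclusion. The conversion to an SD needs the size of the source series, which is not given; an assumed 20 to 40 patients would give 8 × √20 = 36 g to 8 × √40 = 51 g. To get from there to an SD of change of 12 to 25 g, one must also assume correlations of about 0.76 to 0.97, since r = 1 − SD of change² / (2 × SD²). The low powers in the second table thus cannot be derived from the article. The Background percentages are indirect evidence too: they describe incident dialysis patients by category, give no LV mass in grams, and do not describe the patients willing and able to train for home treatment whom this trial enrols.

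It can also be said that the article calls the study a pilot, that the full protocol may hold the missing label and correlation, and that a null result would still come with a confidence interval. The last is true, and it is why a null result should not be called uninformative. The first two do not remove the point: the article prints this input as the basis of a 95% power claim, and it is not the variability of the quantity analysed.

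**Conclusion.** The point holds as a mismatch between the input and the analysis. The only variability figure is a baseline echocardiographic spread, and the endpoint is a change measured by cMR. The stated 32 completers follow approximately from using 8 g as the SD, which is valid for the change only under two unstated conditions: that 8 g is a between-patient SD, and that the correlation is 0.5.

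The stated 95% power is therefore unsupported, and the direction of the error is unknown. If 8 g is a true SD, power runs from 0.77 to above 0.99 for correlations from 0.2 to 0.8. The possibility of a standard error is a question for the sponsor to answer, not a finding. The power figures for SDs of 12 to 25 g show only how sensitive the design is. The primary endpoint and the method of analysis are not affected; the defect lies in the justification of the sample size.

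**What to change.** 1. State whether 8 g is a standard deviation or a standard error, and of what.
2. Replace it with a sourced SD of the 6-month change in cMR LV mass, or with a between-patient cMR SD together with a correlation between baseline and 6 months.
3. Keep the planned 38 enrolled patients and restate the power for 10 g, or the detectable difference, over a range of SDs of change. Use the completers that the plan's own dropout rate implies: 38 × 0.8 = 30.4, about 15 per arm, where an SD of 8 g gives power 0.91.
4. Optionally, once enough patients have both scans, check the SD with a blinded estimate pooled over the arms. The article does not say how many patients have reached that stage. Any treatment effect inflates the pooled estimate: with a true SD of 8 g and a true difference of 10 g it is √(8² + 10²/4) = 9.4 g. It should be read as an upper-leaning figure.

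The cost is a few sentences and, if the option is taken, one blinded calculation. No alpha is spent and no patients are added. The downside is that the restated power may be less favourable than 95%.

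### The 20% dropout allowance covers only the six study months and not the wait between randomisation and baseline, so 19 randomised per arm are not expected to give 32 completers

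*Protocol article*

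**What the plan says.** All references are to the protocol article.

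- **Sizing (Statistical considerations).** The inputs are "the baseline LV mass for both groups will be 147 +/- 8 g" and a two-sided test at 0.05 for a "10 g difference in LV mass", with power 0.95. These lead to 32 patients completing. The allowance for loss is then "Assuming 20% dropout (due to transplantation or death over six months), 19 patients in each arm of the study will be enrolled".
- **Timing of randomisation (Methods/design).** "randomization will occur at one time point for patients willing to enter the study", while the baseline visit, which that section equates with study entry, is staggered afterwards to suit the training programme. Table 1 has separate columns for randomisation and baseline. The quality-of-life section also lists questionnaires at both points.
- **Who is analysed (Statistical considerations, and the footnote to Table 2).** The primary analysis takes enrolled patients with at least one cMR, and the first cMR is at baseline. Patients lost after baseline are kept with zero change.
- **What enrolled means.** The abstract says "Patients enrolled in the study will be randomized to either NHD or CvHD for a six month period". The Table 2 footnote describes the analysis set as randomised subjects, where the text says enrolled patients.
- **Calendar (Procedures – General considerations).** "The first patient was enrolled in August 2004 and by January 2006 enrollment is expected to be complete".

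**The concern.** The allowance and the design use different clocks. The 20% is explicitly a six-month figure, which suits a patient followed from the baseline visit to exit. The design starts counting patients earlier, at randomisation, and then makes some of them wait. During the wait they face the same two causes of loss that the allowance names, and nothing in the sizing covers that interval.

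A loss during the wait also does more damage than a later one. A patient who drops out after baseline stays in the primary analysis under the zero-change rule. A patient who dies or is transplanted before baseline has no cMR, so the rule has nothing to carry forward and the patient disappears from the analysis. The article justifies the staggering as a way to keep drop-out balanced between the arms. That speaks to balance, not to the number lost.

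At stake are the expected number of completers and the 95% power that the plan claims.

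**Working it through.** **Inputs from Statistical considerations:** difference 10 g; SD 8 g (given for baseline LV mass, and the only SD stated); two-sided alpha 0.05; power 0.95; 32 completers (16 per arm); 20% loss over six months; 19 enrolled per arm. Whether a baseline SD suits a change score is a separate question and is not needed here.

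**1. The plan's own figure.** By the normal formula, n per arm = 2 × [8 × (1.960 + 1.645) / 10]² = 16.6, which rounds up to 17 per arm, or 34 in total. The stated 32 is close. At 16 per arm, power is 94.2% by the normal formula and 92.8% by the t-test. The t-test is used below.

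**2. No wait.** Completers = 19 × 0.8 = 15.2 per arm, or 30.4 in total, with power 91.4%. To keep 32 of 38, total loss may not exceed 6/38 = 15.8%, so the stated 20% already uses up all the slack. (Full inflation would be 16/0.8 = 20 per arm. That is a separate and smaller matter.)

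**3. Adding the wait.** The documents do not give its length, so this step rests on assumptions: the plan's rate also applies while waiting, and entries are spread evenly from 0 to W months.

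- Monthly rate: λ = −ln(0.8)/6 = 0.0372.
- Mean probability of reaching baseline: p(W) = [1 − exp(−λW)] / (λW).
- Completers per arm: 19 × p(W) × 0.8.

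| Longest wait W | p(W) | Completers per arm | Total | Power (t-test, completers) | Cost of the wait | To randomise per arm for 16 completers |
|---|---|---|---|---|---|---|
| 0 | 1 | 15.2 | 30.4 | 91.4% | – | 20 |
| 3 months | 0.946 | 14.4 | 28.8 | 89.8% | 1.6 points | 22 |
| 6 months | 0.896 | 13.6 | 27.2 | 88.0% | 3.4 points | 23 |
| 12 months | 0.807 | 12.3 | 24.5 | 84.2% | 7.2 points | 25 |

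**4. Sensitivity to the rate during the wait.** The Background section gives mortality of nearly 20% per year. Applying only that during the wait, with no transplants, means λ = −ln(0.8)/12 = 0.0186 before baseline and the plan's 20% afterwards. Longest waits of 6 and 12 months then leave 14.4 and 13.6 completers per arm (28.8 and 27.2 in total), with power about 90% and 88%.

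**5. Sensitivity to the rate throughout.** At half the plan's rate (10% per six months) both before and after baseline, a 6-month spread leaves 19 × 0.949 × 0.9 = 16.2 per arm, which meets the 16 required. A 12-month spread leaves 19 × 0.902 × 0.9 = 15.4.

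**6. The planned primary analysis.** Steps 2 to 5 count completers only. As an illustration of the zero-change rule, suppose 20% of each arm is set to no change, the true change is 10 g in one arm and 0 in the other, and the SD is 8 g. The mean difference becomes 0.8 × 10 = 8 g. The variances are 0.8 × 64 + 0.16 × 100 = 67.2 and 0.8 × 64 = 51.2. With 19 per arm, SE = √(118.4/19) = 2.50 and normal-approximation power is about 89%. With 10% lost before baseline (17.1 per arm), SE = √(118.4/17.1) = 2.63 and power is about 86%.

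**The case against.** The strongest reply is that enrolled may not mean randomised in the sizing sentence. If the 19 per arm are patients who have reached the baseline visit, six months is the right window and the sizing has no gap. The calendar sentence in Procedures – General considerations can be read that way. This reply partly stands, because the article never says outright which is meant. The abstract, the analysis-set sentence (which implies that some enrolled patients have no cMR) and the Table 2 footnote all lean towards randomised. On the other reading, the article gives no number to be randomised.

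A reader might infer from the calendar sentence that some patients waited up to 17 months, which on the same assumptions would leave 11.3 completers per arm and power of 81%. The documents do not support that. If enrolment means randomisation, those dates describe when patients were randomised and say nothing about how long anyone waited. If it means baseline entry, the 19 per arm may well be baseline entrants too.

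A reader might also conclude that 19 per arm cannot produce 32 completers, or that the lost patients cannot be replaced. Neither follows. At half the plan's attrition and a 6-month spread, 16.2 per arm complete, and no passage bars further recruitment.

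Two further points stand. The 95% is missed with no wait at all, so only the difference from 91.4% belongs to the wait. And completer power is not the power of the planned primary analysis, although the zero-change rule does not raise it and cannot recover a patient without a baseline scan.

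Finally, a condensed article may leave the entry schedule to the full protocol, so its absence is no fault. The point here is the window that the sizing sentence does state.

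**Conclusion.** The point holds in a conditional form. If the 19 per arm are randomised patients, the sizing uses too short an exposure window, and 32 completers are not expected under the plan's own 20%. The expected number is 30.4 with no wait. It is about 28.8, 27.2 or 24.5 with waits spread evenly up to 3, 6 or 12 months, with completer power of about 90%, 88% or 84% against 91% without a wait. The part due to the wait is therefore about 2 to 7 points.

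These sizes rest on assumed waits, a constant loss rate equal to the plan's 20% per six months, and the plan's 10 g and 8 g. The direction is firmer than the size: any loss before baseline comes off a sample with no slack, and using only the article's background mortality during the wait leads to the same conclusion. The shortfall disappears only if attrition is well below what the plan assumes, or if enrolled means having reached baseline.

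**What to change.** In Statistical considerations, take one of two courses:

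- **If 19 per arm are randomised patients:** define attrition from randomisation to the exit cMR, covering the wait as well as the six months, and restate the expected completers and the power. State the assumed waits. No extra enrolment is needed if the power is restated.
- **If 19 per arm are patients who reach the baseline cMR:** say so, and give the number to be randomised. For scale, 16 completers per arm would need about 22, 23 or 25 randomised per arm for the 3-, 6- or 12-month spreads above.

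Use the same meaning of enrolled in the abstract, the calendar sentence, the analysis-set sentence and the Table 2 footnote. Either course takes a sentence or two. The first brings a less favourable stated power. The second makes explicit that more patients must be randomised than the article now shows.
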